#### C. Outcomes to be Measured

**Primary outcome(s):**

[figure not shown]

- (a) The clusters of multimorbidity\*; and,
- (b) The multimorbidity cluster trajectories throughout the follow up period.

\*Multimorbidity will be defined as the presence of two or more long-term conditions (out of the clinical consensus-derived 220 conditions described in appendix 1) within the same individual. Unsupervised machine learning algorithms applied to the dataset will then derive and define clusters of multimorbidity, by grouping similar entities together (using an understanding of difference in distance between data points). A sample of code sets used to select conditions are shown in Appendix 2.

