Little is known about variation in multimorbidity between ethnic groups across the UK, but early studies suggest an important impact on the conditions included in multimorbidity clusters, as well as the trajectories to these clusters during the life course. In east London, British south Asians are twice as likely to have cardiovascular multimorbidity than White people (6). Black Africans and Black Caribbeans are reported to have similarly high rates of multimorbidity including diabetes and depression in south London (7). In both studies, ethnicity and socioeconomic deprivation were strongly co-correlated, highlighting the importance of looking across wider populations that are representative within the UK and relevant to wider global populations. Furthermore, ethnic minority groups are disproportionately impacted by conditions such as HIV and some cancers that may independently influence risk of multimorbidity. Our work will embed analyses to ensure that ethnic variation in multimorbidity is adequately assessed and understood.

Our analyses will utilise a combination of standard epidemiological analyses and machine learning techniques to describe prevalence patterns of multimorbidity conditions and their longitudinal progression. Our research will also build on increasingly used data-driven clustering techniques that support unbiased characterisation of structures/relationships between objects (in this case clinical conditions). By applying these techniques to a more extensive, and consensus-built list of clinical conditions that could contribute to multimorbidity, we expect to elucidate novel clusters unbiased by a priori knowledge or clinical selection. The multimorbidity clusters that we identify will be characterised further through analysis of their trajectories across the lifecourse, their determinants, and their associations with prescribing/polypharmacy and healthcare utilisation.

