## N. Data/ Statistical Analysis

### Research Aim A)

We will estimate the prevalence of each condition included in our consensus-built list of 220 conditions across sex, age groups and ethnic groups (White, Black African and Caribbean, and south Asian). We will also describe the presence of multimorbidity ( $\geq 2$  conditions) across different sociodemographic characteristics (age, sex, ethnic groups and deprivation level).

We intend to apply unsupervised machine learning techniques to identify clusters of multimorbidity across an unselected population, and within specific ethnic groups. Recent research suggests that unsupervised learning techniques have potential to identify novel patterns and relationships from electronic health records and reveal latent disease clusters and patient subgroups (16). We will potentially use the overlapping technique, which allows each disease to belong to two or more clusters that present separate degrees of membership. The advantage of using this type of clustering is that the diseases on the boundaries between several clusters are not forced to fully belong to a single cluster, but rather are assigned membership degrees between 0 and 1 indicating their partial membership (17,18). We may apply a prevalence-based revision of the conditions included in our multimorbidity clusters (as used by Kuan and colleagues (2) who set a prevalence cut off of 0.01% in their data-driven analysis) if there is concern that very low prevalence conditions are subject to reporting bias or poor data quality.

We will describe the patterns of multimorbidity by calculating the frequencies and percentages of conditions within each cluster, and diseases will be assigned to the cluster in which they present the highest membership value. The membership value will be estimated using the ratio between the disease prevalence within the cluster by the disease prevalence in the overall population (19). We will examine how clustering varies in the context of more prevalent conditions (e.g. diabetes, hypertension, depression) compared to less prevalent conditions (e.g. HIV and cancer).

We will use the CPRD Aurum as a validation data set, aiming to replicate our methods and validate our findings in an ethnically-diverse East London population.

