### Research Aims B)

To characterise the trajectory of multimorbidity clusters across the life course, we will identify clusters of multimorbidity and trace their evolution from single index conditions, and their trajectories across the lifecourse, including to death, over ten years. We anticipate focusing this analysis on up to 8 multimorbidity clusters, selected to ensure we generate new knowledge, e.g. clusters which include less-studied conditions such as cancer or HIV, as well as those where there is variation by ethnicity. We will follow the individuals within the selected clusters to identify the acquisition of new conditions and potentially changes in the cluster they belong to over time. Our analysis will consider how these trajectories to multimorbidity vary according to different 'index conditions', e.g. diabetes, HIV and cancer.

The assessment of the sequence of multimorbidity clusters an individual belongs to over the years will allow us to understand their disease trajectory over the period they were under observation and at different points in time. The multimorbidity cluster trajectories assessment will take into account the individuals' socioeconomic characteristics, potential risk factors and time dependent variables (e.g. clinical measurements, health seeking behaviours, health care utilisation, and life events).

[figure not shown]

We will identify individuals who share similar patterns of multimorbidity using clustering algorithms at different points in time. We aim to assess at least three points in time, with a ~five year interval between them (e.g. Jan 2011, Jan 2016 and Dec 2020). This time window will be subject to revision according to the available follow-up time in years of our study population. To evaluate the multimorbidity cluster trajectories, each individual will be assigned to the cluster with the highest membership degree in each point in time. We will be able to identify how the multimorbidity cluster changes in individuals from different age groups, sex and ethnicity.

We will estimate the association between the multimorbidity clusters and the risk to mortality in each follow-up period using Cox models adjusted by socioeconomic characteristics (age, sex, IMD) and risk factors (clinical measurements, health seeking/risk behaviours, health care utilisation, and life events) some of which are time dependent variables (e.g. BMI, blood pressure, lipids, HbA1c).

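### High within-cluster ratios and agreement with Aurum do not by themselves show that conditions co-occur beyond prevalence and age; a permutation reference would supply the missing comparison cheaply.

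*Protocol*

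**What the plan says.** Section C of the protocol lists the clusters themselves as primary outcome (a) and leaves their definition to the method: "Unsupervised machine learning algorithms applied to the dataset will then derive and define clusters of multimorbidity".

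Section N, Research Aim A, then fixes three things:

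- The statistic: "The membership value will be estimated using the ratio between the disease prevalence within the cluster by the disease prevalence in the overall population".
- The assignment rule: "diseases will be assigned to the cluster in which they present the highest membership value". No minimum value is given.
- The validation, in CPRD Aurum: "aiming to replicate our methods and validate our findings in an ethnically-diverse East London population".

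The algorithm itself is left open. Overlapping (fuzzy) clustering is named only as a possibility.

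The population to be clustered is not consistently described. Section N (Aim A) speaks of an unselected population, and section H includes people whether or not they are multimorbid. Section K restricts the population to those who ever had a recorded multimorbidity condition.

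On interpretation, section E states: "we expect to elucidate novel clusters unbiased by a priori knowledge or clinical selection". On use, section N (Aim B) states: "We anticipate focusing this analysis on up to 8 multimorbidity clusters", and Aim C expects to work on the same clusters.

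**The concern.** The protocol will present a high ratio, and recurrence of the cluster in Aurum, as the description and validation of a cluster. Both can arise when no two conditions are associated. A group made of people who share one common condition has a high ratio for that condition simply because it was formed on it, and the same group can be expected wherever that condition is similarly common.

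Other provisions do not fill the gap. Stratification by sex, age and ethnic group (section O) addresses confounding and gives no picture of what chance and prevalence alone would produce. The optional prevalence cut-off in section N is aimed at reporting bias and data quality. Section T concedes that the solution depends on which conditions are included, but not that groups can appear without association.

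At stake is which of the selected clusters, carried into the trajectory, mortality and prescribing analyses, can be described as novel disease associations rather than groups around common conditions.

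**Working it through.** **The plan's own figure.** Section I: n = Z²P(1−P)/d² = 1.96² × 0.272 × 0.728 / 0.002² = 190,174.6, which reproduces the stated 190,174. It concerns the precision of one prevalence and says nothing about whether clusters are real.

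**Inputs from the protocol.** 220 conditions; 27.2% multimorbid; ratio and highest-value rule (section N); up to 8 clusters.

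**Assumed inputs.** The spectrum of condition prevalences, the number of clusters, and the algorithm (k-means, then fuzzy c-means). 50% multimorbid was also tried, because 220 conditions are counted rather than 36.

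**Step 1: what the ratio does by construction.** Let w_j be the share of people in cluster j, q_j the prevalence of a condition in it, P its overall prevalence, and r_j = q_j/P.

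- If the clustered and reference populations are the same, Σ w_j r_j = 1. The highest r_j is therefore at least 1 for every condition.
- If a cluster consists of carriers of one condition, q_j = 1 and r_j = 1/P. A prevalence of 0.10 gives 10.
- If only people with two or more conditions are clustered but P is the whole-population prevalence, Σ w_j r_j = S, where S = P(at least one other condition)/P(at least two conditions). The highest ratio is then at least S.

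**Step 2: the size of S under independence** (Poisson approximation, mean m conditions per person, condition not itself common).

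- 27.2% multimorbid: m = 1.02, since 1 − e^(−1.02) × 2.02 = 0.272. S = (1 − e^(−1.02))/0.272 = 0.639/0.272 = 2.35. Simulation gave about 2.4.
- 50% multimorbid: m = 1.678. S = (1 − e^(−1.678))/0.5 = 0.813/0.5 = 1.63. Simulation gave 1.64.

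**Step 3: null simulations, k-means, all 220 conditions independent, clustering the multimorbid.**

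- At 29.6% multimorbid with 8 clusters, seven were each built on one condition present in 100% of members. A separate run at 29.7% gave the same.
- Clusters containing a condition with a ratio of at least 2 against the *multimorbid* population: 7 to 8 of 8, and 14 of 15. In the best-optimised runs the largest ratio was 8.6 to 18.9.
- Individual conditions reaching 2 at 29.6% multimorbid: 220 of 220 against the whole population, but only 7 (8 clusters) or 17 (10 clusters) against the multimorbid. When the unselected population was clustered, separate runs gave 90 and 97 of 220.
- The 220 of 220 needs no clustering. With 1.08 conditions per person, a top prevalence of 16% and 29.6% multimorbid, even the commonest condition has S of at least (1 − e^(−0.92))/0.296 = 0.601/0.296 = 2.03.

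**Step 4: replication of noise clusters in a second independent dataset.**

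| Setting | Agreement |
|---|---|
| Same prevalences, best optimum found | adjusted Rand index 1.00 |
| Prevalences shifted (log-SD 0.3), best optimum found | 0.65 to 1.00 |
| Random starts only, skewed prevalences | 0.33 to 0.85 |
| Random starts only, flat prevalences | 0.10 to 0.56 |
| Same prevalences, matched centroids | median cosine 0.92 (8 clusters), 0.84 (10 clusters) |

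The best optima came from starting the search at the commonest conditions, which beat the random starts in every such run.

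**Step 5: fuzzy c-means, 8 clusters, independent conditions, clustering the multimorbid.**

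- Fuzzifier 1.5 and 2.0: in one set of runs all centroids coincided and every membership was 1/8 = 0.125. In another, at 1.2 and 2.0, many clusters merged, but the main survivors were largely single-condition groups that matched a second noise dataset at 0.97 to 1.00.
- Fuzzifier 1.1: at 27% multimorbid, six of eight clusters had one condition in 100% of members, and two noise datasets matched with median cosine 0.97. In a separate run the median top membership was 0.52.
- On data built with real correlation, fuzzifiers 1.5 and 2.0 collapsed in the same way.

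**The case against.** Five arguments deserve weight.

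1. *A statistical analysis plan may contain validity checks.* True, so the mere absence of a null reference is not the point. The point rests on what the protocol states: the ratio, the highest-value rule, the unclear population and replication as validation.

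2. *K-means is not the method named for Aim A.* Also true; it is listed for Aim C. The reference cited for overlapping clustering is fuzzy c-means, which can return nothing from noise. A reader might infer that clustering always manufactures groups; that is wrong. But collapse is no test of association, because it also occurred when correlation was present. At a fuzzifier that does return groups, noise groups mostly replicated.

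3. *The finding that all 220 conditions reach a ratio of 2 is a denominator effect.* Correct. It does not apply if the unselected population of section N is clustered. A uniform inflation also leaves unchanged which cluster a disease is assigned to.

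4. *Aurum could expose artefacts.* In part. East London may have a different prevalence mix, and poorly optimised noise solutions replicate badly. That poor agreement reflects the search rather than association, so replication in either direction remains hard to read.

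5. *The study is descriptive and hypothesis-generating (section F).* Section E expects groups around common diseases, and Aim B clusters are chosen for less-studied conditions or ethnic variation. This lowers the stakes, but the wording on novel, unbiased clusters still needs a basis.

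**Conclusion.** The point holds in a limited form. A high within-cluster ratio and agreement with Aurum are compatible with independent conditions, so neither is in itself evidence of co-occurrence beyond prevalence and age. With 8 k-means clusters, 7 or 8 noise clusters passed a ratio of 2 against the multimorbid. The mixed denominator alone adds a factor of about 2.4 (27.2% multimorbid) or 1.6 (50%).

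These sizes rest on assumed prevalences, numbers of clusters and tuning, none of which the protocol fixes.

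A reader might go further and infer that the planned clusters will be artefacts, or that the Aurum replication is worthless. The documents do not support that. Real disease clusters may well be present in these data, the algorithm is still open, and replication remains useful for stability. What is missing is the comparison that would tell the two kinds of cluster apart. Label: cheap improvement.

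**What to change.** Add to section N (Aim A):

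- Compute the ratio with the same population in numerator and denominator, and state which population is clustered, reconciling sections H, K and N.
- Re-run the chosen algorithm, with the same tuning, on a stated number of datasets in which each condition is permuted independently among patients within age band × sex (× ethnic group). Apply any two-condition selection after permuting.
- Report observed ratios and cluster separation beside this reference, in GOLD and in Aurum. Comparing each condition's highest ratio with its own highest ratio in the permuted runs avoids matching clusters across runs.
- Describe a cluster as a novel disease association only where it exceeds the reference, and give the size of the excess.

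Do not make a fixed percentile a condition for entering Aim B. With about 3 million people even trivial association may pass it, so it would probably exclude little, and Aim B has its own selection reasons.

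Cost: computing time and protocol wording; no new data. The downside is that some clusters will be reported as no more than expected from prevalence and age.

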#### Secondary outcomes:

- (a) Index condition to multimorbidity cluster; and,
- (b) Multimorbidity cluster to death

### D. Objectives, Specific Aims and Rationale

Our strategic objective is to understand multimorbidity clusters and their trajectories through the application of advanced data analysis. We seek to expand on existing multimorbidity studies by incorporating a broad set of health conditions, selected by a rigorous clinical consensus exercise (see Appendix 1). We will meet our objectives through the use of a large, high quality electronic health record (EHR) dataset representative of the UK population.

Our specific research aims are as follows:

- A) To characterise multimorbidity clusters using data-driven methodology that expands current definitions and broadens relevance to ethnic minorities;
- B) To characterise the trajectory of multimorbidity clusters across the life course to death, and to describe their determinants;
- C) To describe the relationship between the patterns of multimorbidity identified in A) and B) with prescribing/polypharmacy.

**Rationale:** The need to better understand and describe patterns of multimorbidity has been acknowledged by the recent Academy of Medical Sciences report (4). This report highlights the need to build on existing studies of multimorbidity (which mostly use a limited set of ~40 single conditions, based on the original work by Barnett et al (5)), and expand the definition of multimorbidity to incorporate a wider set of chronic conditions. There is also a lack of knowledge of how multimorbidity varies according to ethnicity, and early studies suggest significant differences, e.g in east London, British south Asians are twice as likely to have cardiovascular multimorbidity than White people (6). Black Africans and Black Caribbeans are reported to have similarly high rates of multimorbidity including diabetes and depression in south London (7). Most existing studies of multimorbidity use cross-sectional data to estimate prevalence and there is limited knowledge on the longitudinal trajectories from single 'index' conditions to multimorbidity, what their determinants are, and what their wider impact is on prescribing and healthcare utilisation.

Combining powerful, data-driven analysis methods with high-quality, linked electronic health record data from a nationally-representative dataset, offers an opportunity to build on these knowledge gaps and develop a new understanding of multimorbidity.

### E. Study Background

Multimorbidity is increasingly recognised as an important research priority, due to its increasing prevalence and its significant burden on health, health systems, and society in the UK and globally. However, the recent Academy of Medical Sciences report (4) identifies the significant gaps in our knowledge of multimorbidity, and highlights the need to define broader clusters of multimorbid conditions, study their development during the life course, and understand their association with ethnicity and social deprivation.

Most existing multimorbidity research includes a maximum of ~40 single conditions using diagnoses whose recording in EHR is incentivised through the Quality and Outcomes Framework for NHS primary care (3,5,8).

[figure not shown]

However, these definitions fail to include numerous conditions known to closely cluster with other conditions and with high impact to the individual and health services. Examples of such conditions that are understudied in existing multimorbidity research include human immunodeficiency virus (HIV) and cancer, and these may underlie some ethnic variation in multimorbidity (9). High quality, large-scale electronic health record data, e.g. from CPRD, offers an exciting opportunity to build on existing definitions of multimorbidity and expand their scope using advanced data analysis. We propose doing so by incorporating a larger set of chronic conditions (n~200) for inclusion, defined through a rigorous consensus-building exercise (see Appendix 1), and through the application of data clustering techniques that can support high-throughput and data-driven analyses. We will undertake entirely data-driven, unbiased clustering of all ~200 conditions. We anticipate identifying multimorbidity clusters based around common chronic diseases such as diabetes and hypertension but will additionally examine the performance of our multimorbidity clustering around a limited number of specific low- and medium-prevalence conditions (HIV and specific cancers, respectively), selected due to their high health impact, disproportionate impact on minority ethnic groups and increasing relevance to multimorbidity research (primarily due to increasing survival rates).

Currently, most studies of multimorbidity use cross-sectional data sources and rarely characterise its emergence or trajectory across the life course. In the limited number of studies where these longitudinal analyses have been performed, important insights into the risk factors and potential causation of multimorbidity have been derived. For example, in a modest sample from Whitehall II cohort study data (n=8,270) with low rates of multimorbidity (6.6%) at age 50 years, an association between socioeconomic status and progression to multimorbidity was identified, but with unclear influence from clinical risk factors (10). Knowledge is needed from larger population-based longitudinal studies to better understand the trajectories to the development of multimorbidity clusters from risk factors and single index conditions. Electronic health records, particularly where linked data are available, also offer the ability to study trajectories across important life course events such as pregnancy, and to death. It is also important to consider the wider impact of multimorbidity on individuals experiencing it and health systems. Recent work using cross-sectional CPRD data identifies a close relationship of multimorbidity with number of prescriptions and healthcare use (11). Investigating these wider interrelationships further, e.g. by more detailed analysis of prescription data and using longitudinal data, offers the potential to elucidate causal relationships (e.g. between multimorbidity and the use of specific drugs) (12) and to identify opportunities for early detection and intervention.

Little is known about variation in multimorbidity between ethnic groups across the UK, but early studies suggest an important impact on the conditions included in multimorbidity clusters, as well as the trajectories to these clusters during the life course. In east London, British south Asians are twice as likely to have cardiovascular multimorbidity than White people (6). Black Africans and Black Caribbeans are reported to have similarly high rates of multimorbidity including diabetes and depression in south London (7). In both studies, ethnicity and socioeconomic deprivation were strongly co-correlated, highlighting the importance of looking across wider populations that are representative within the UK and relevant to wider global populations. Furthermore, ethnic minority groups are disproportionately impacted by conditions such as HIV and some cancers that may independently influence risk of multimorbidity. Our work will embed analyses to ensure that ethnic variation in multimorbidity is adequately assessed and understood.

Our analyses will utilise a combination of standard epidemiological analyses and machine learning techniques to describe prevalence patterns of multimorbidity conditions and their longitudinal progression. Our research will also build on increasingly used data-driven clustering techniques that support unbiased characterisation of structures/relationships between objects (in this case clinical conditions). By applying these techniques to a more extensive, and consensus-built list of clinical conditions that could contribute to multimorbidity, we expect to elucidate novel clusters unbiased by a priori knowledge or clinical selection. The multimorbidity clusters that we identify will be characterised further through analysis of their trajectories across the lifecourse, their determinants, and their associations with prescribing/polypharmacy and healthcare utilisation.

This discrete project will link to two interrelated and synergistic research projects already underway, funded through the recent strategic UKRI multimorbidity funding streams. First, an MRC grant awarded to the lead applicant (with [name] as Co-Investigator) studying "Multimorbidity clusters, trajectories and genetic risk in British south Asians", and second, an NIHR AIM Development award (led by [name], with [name] and [name] as Co-Investigators), which aims to characterise the dynamic inter-relationships between multimorbidity and polypharmacy using artificial intelligence.

More distally, our work will build on methodological expertise relevant to a growing body of research on multimorbidity and polypharmacy, and other health data science projects that will build capacity and support future research in this area. This project is therefore likely to support, indirectly, related funded programmes elucidating

[figure not shown]

genetic causes of multimorbidity: the Wellcome Trust-funded Genes & Health study, and collaborative work with the Lifespan multimorbidity research Collaborative, currently funded by an MRC Development award.

